### Unblinding

After all the data has been verified and locked, the principal researchers, statisticians, and sponsors are responsible for the statistical analysis plan. When removing the blindness for the first time, it will indicate the group to which the patient belongs (only either group A or group B will be assigned to each patient). Any modification to the database is possible only by joint written agreement between the head of clinical researchers, statisticians, and data administrators. The first level blind codes will be handed over to the statisticians for statistical analysis according to the statistical analysis plan. Finally, the statistical analysis report will be developed by the statisticians, and the second unblinding (that is, the patient belongs to the control or intervention group) will be performed at the summary meeting.

### Statistical Analysis

#### Definition and Selection of Statistical Analysis Data Set

The subjects in the trial will be categorized as follows:1. Full Analysis Set (FAS)

FAS is defined as the data set composed of all subjects who are block randomized and have at least one efficacy evaluation result after baseline, which is the main analysis set for efficacy evaluation. Demographics and other baseline characteristics are also set as the FAS. The missing value of the primary efficacy indicators will be filled with the last observation carried forward. In comparison, the missing values of secondary efficacy and safety indicators will not be filled.2. Per Protocol Set (PPS)

PPS comprises all the FAS subjects who meet the inclusion criteria but not the exclusion criteria and complete the treatment protocol without seriously violating the study protocol, which is the secondary analysis set for efficacy evaluation.3. Security data set (Safety Set, SS)

SS includes all subjects who are block randomized, receive at least one dose of Mudan granule, and have at least one postbaseline safety evaluation.

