### Withdrawal Criteria

#### The Withdrawal Decided by the Researcher

The researcher can decide to withdraw a subject from the study under the following circumstances:1. During the study, the subjects may develop severe acute or chronic complications or special physiological changes (e.g., human chorionic gonadotropin test is positive) that not appropriate for this study.2. During the study, the subjects may have poor adherence to medications, such as failure to take less than 80% or more than 120% of the prescribed dosage.3. Other treatment drugs were added without following the researcher’s guidance during the entire study period.

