### Sample Size Calculation

Depending on the previous study (Li and Yu, 2016) of Mudan granule combined with methylcobalamin in the treatment of DPN with 12 weeks intervention, the results of the MDNS indicated that the study group (Mudan granule + Methylcobalamin) scale score was 5.48 ± 1.19, the control group (Placebo + Methylcobalamin) scale score was 8.21 ± 1.24, and the mean difference between the two groups was 2.73; Assuming that Mudan granule combined with methylcobalamin in the treatment of DPN can reduce the MDNS by 0.58 after 12 weeks of intervention, it is considered more effective than the control group. Taking *α* = 0.05, *β* = 0.10, the intervention group and the control group with 24 weeks intervention were allocated at a ratio of 1:1. The sample size calculated by the Power Analysis and Sample Size (PASS) 11 software is not less than 167 cases in each group. Considering that an expected withdrawal rate does not exceed 20%, the target sample size is set at 402, with 201 cases in each group.

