### Statistical Analysis Method

SAS 9.4 will be employed for statistical calculations. All data statistics will be analyzed by using a bilateral test, and *p* ≤ 0.05 suggested statistical significance. Count data will be expressed by the constituent ratio. The description of the quantitative data will use the mean, standard deviation, median, and minimum/maximum values. All indicators will be analyzed using appropriate statistical methods. Comparisons between groups of quantitative data will be performed using the Wilcoxon rank-sum test and group *t*-test. The main efficacy indicators will be described with the diachronic statistical description. Analyses of covariance with baseline as a covariate will be used to adjust for comparisons between groups. If necessary, the center effect may be considered and the least square means (LS-means) with their 95% confidence intervals (95% CI) for each group will be calculated. Chi-squared or Fisher’s exact test will be used for categorical data, while grade data will be analyzed by the CMHχ^2^ test or Wilcoxon rank-sum test.

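### Secondary scales measured repeatedly are left unfilled and compared only by single-visit methods, so subjects with earlier scores but no week-24 value would drop out of a week-24 comparison

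*Protocol article*

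**What the plan says.** The section on analysis data sets in the protocol article treats the two classes of efficacy outcome differently. For the MDNS, "The missing value of the primary efficacy indicators will be filled with the last observation carried forward". For the rest, "the missing values of secondary efficacy and safety indicators will not be filled". The main efficacy set is the FAS: randomised subjects who "have at least one efficacy evaluation result after baseline, which is the main analysis set for efficacy evaluation".

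The Statistical Analysis Method section names the methods for quantitative data: "Comparisons between groups of quantitative data will be performed using the Wilcoxon rank-sum test and group *t*-test" and "Analyses of covariance with baseline as a covariate will be used to adjust for comparisons between groups". It names no longitudinal model.

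The Secondary Outcomes section gives these schedules:

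- **TCSS and clinical symptom scores:** baseline, weeks 12 and 24.
- **TCM syndrome score:** baseline and every 4 weeks to week 24.
- **NCV and corneal measures:** baseline and week 24 only.

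The sample size section plans for withdrawal: "an expected withdrawal rate does not exceed 20"%.

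**The concern.** A t-test, a rank-sum test or an ANCOVA on baseline at week 24 uses only subjects with a week-24 value. A subject seen at week 12 and lost afterwards belongs to the FAS but contributes nothing to that comparison. For the TCM syndrome score, up to five post-baseline scores (weeks 4, 8, 12, 16 and 20) go unused.

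Two things are at stake. Precision is lost in any case. Bias arises if withdrawal is related to the interim score and that relation, or the withdrawal rate, differs between arms. Withdrawal need not be random: one ground on which the researcher may withdraw a subject is that "the subjects may have poor adherence to medications", and others are complications and unguided added drugs. The study hypothesis includes relief of clinical symptoms, which these scales measure.

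**Working it through.** **Inputs from the protocol article.** 201 per arm; withdrawal up to 20%; visits as listed above; two-sided 5% level. The article gives no figure for the secondary outcomes. Its withdrawal allowance reproduces as 167 × 1.20 = 200.4, rounded up to 201.

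**Step 1. Subjects lost at week 24.** 201 × 0.20 = 40.2, so up to about 40 per arm have no week-24 value. 201 × 0.80 = 160.8, so about 161 per arm remain.

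**Step 2. Bias, by simulation.** The documents do not give the following, so it is assumed: SD 1; correlations baseline–week 12 0.6, baseline–week 24 0.5, week 12–week 24 0.7; normal scores; no true effect; 20% missing at week 24 in each arm; every dropout has a week-12 score; dropout depends on that score through the odds ratio per SD shown. 4,000 trials per row.

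| Odds ratio, arm 1 / arm 2 | Completer ANCOVA bias (SD) | Rejection under the null |
|---|---|---|
| 1 / 1 | 0.001 | 4.6% |
| 2 / 1 | 0.051 | 8.5% |
| 3 / 1 | 0.075 | 12.0% |
| 2 / 0.5 | 0.106 | 19.9% |

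The likelihood-based repeated-measures estimate stayed within 0.002 SD of zero in every row. A separate simulation of the dependent-dropout rows gave about 0.05, 0.08 and 0.10 SD, with about 8%, 11% and 19% rejection. When dropout acted alike in both arms, the repeated-measures standard error was about 2% to 4% smaller.

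**Step 3. Check by formula.** The standard error of completer ANCOVA is about √(1 − 0.5²) × √(2/161) = 0.866 × 0.1115 = 0.0965 SD. Rejection is Φ(−1.96 + b/SE) + Φ(−1.96 − b/SE), where b is the bias.

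- b = 0.051: b/SE = 0.528, rejection 8.3%.
- b = 0.075: b/SE = 0.777, rejection 12.2%.
- b = 0.106: b/SE = 1.098, rejection 19.6%.

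These agree with the simulated rates.

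**Step 4. Range over other assumptions.** A large-sample run (400,000 per arm) used baseline correlations of 0.5 to 0.6, week 12–week 24 correlation of 0.5 to 0.8 and a log-odds slope of 1 per SD. Completer bias was:

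- about 0 when dropout was completely at random, or had the same rate and dependence in both arms;
- 0.05 to 0.08 SD when dropout depended on the score in one arm only;
- 0.04 to 0.08 SD with the same dependence but 10% against 30% dropout;
- 0.09 to 0.16 SD with opposite dependence.

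At 10% dropout, the one-arm biases roughly halve, to about 0.025 to 0.04 SD.

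**Step 5. Dropouts before week 12.** Here half the dropouts are assumed to leave before week 12, driven by the same underlying course.

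| Odds ratio, arm 1 / arm 2 | Completer bias (SD) | Repeated-measures bias (SD) | Share remaining |
|---|---|---|---|
| 2 / 1 | 0.052 | 0.023 | 44% |
| 3 / 1 | 0.078 | 0.036 | 46% |
| 2 / 0.5 | 0.108 | 0.048 | 44% |

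The earlier visits therefore remove a little over half of the bias in this case.

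**The case against.** **The sentence on missing values is not an error.** This stands. A mixed model fills nothing either and complies with it. A reader might infer that the article should have imputed these outcomes; nothing in it supports that. The point is only the combination with single-visit methods.

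**The analysis plan may name a better model.** The article refers to a predefined plan, promises suitable methods for all indicators, assigns no test to a given scale and names no comparison week. Week 24 is indeed an inference, though a well-supported one: treatment lasts 24 weeks and every efficacy schedule ends there. The rest carries less weight, because the article does more than stay silent. It fixes the missing-data rule and lists single-visit comparisons. Leaving missing values to a blind review after data entry is not a prespecified remedy.

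**The bias needs unequal dropout.** This stands. The trial is double-blind, both arms receive methylcobalamin, poor response is not a listed ground for researcher withdrawal, and 20% is a ceiling. Sharply different dropout is possible but not shown. Against the planned primary effect of about 0.58/1.215 = 0.48 SD, biases of 0.05 to 0.10 SD are modest.

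**The earlier visits would not fully prevent the bias.** This stands, as Step 5 shows. TCSS and symptom scores have no post-baseline visit before week 12.

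**A Gaussian model may not suit 0–6 symptom scores.** This stands in part. The article sends graded data to CMH or Wilcoxon, and the simulations used normal scores only.

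**Conclusion.** The concern holds in a limited form. Followed as written, the plan would drop up to about 40 subjects per arm from a week-24 comparison of the repeated scales, including those whose earlier scores are on file. The certain cost is small, about 2% to 4% in standard error. Bias of about 0.05 to 0.10 SD, with about 8% to 19% false rejection, arises only if dropout depends on the interim score differently by arm; more extreme assumptions reach 0.16 SD. All these figures rest on assumed correlations and dropout patterns.

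A reader might infer that the secondary results will be biased, or that the earlier visits would cure the problem. The documents support neither: they give no evidence of unequal dropout, and the repair depends on missing at random. The point does not extend to NCV or corneal measures, which have no intermediate visit, and it does not concern the primary outcome's separate rule. It is a worthwhile, inexpensive improvement to secondary analyses.

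**What to change.** In the sections on analysis data sets and statistical methods, state that TCSS and the TCM syndrome score will be analysed on all observed visits with a likelihood-based mixed model for repeated measures. The terms are treatment, visit, treatment-by-visit, baseline, baseline-by-visit and centre, with unstructured covariance, and the week-24 contrast is the result. Treat the 0–6 symptom scores the same way, or with an ordinal repeated-measures model if they are analysed as graded data. Fix this in advance rather than at the blind review, and add a sensitivity analysis for data missing not at random. NCV, corneal and safety outcomes can stay on observed values.

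The cost is some wording and a little programming in the SAS 9.4 already planned, with no new data or visits. The downside is the missing-at-random assumption and the incomplete protection for subjects who leave before their first post-baseline score (week 12 for TCSS and symptoms).

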### Intervention Measures

All included subjects will accept conventional therapies containing 0.5 mg oral methylcobalamin tablets three times per day, lifestyle interventions, and other oral drugs to achieve stabilization of blood sugar, blood pressure, and lipids depending on American Diabetes Association guidelines. Subjects will be randomly allocated to either the intervention group (Mudan granule 7 g/bag, three times per day) or the control group (placebo 7 g/bag, three times per day) through a central randomization system. Treatment will continue for 24 weeks.

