### Blinding

This trial is conducted as a double-blind study. In this double-blind clinical study, researchers, subjects, monitors, statisticians, and data administrators are unaware of the treatment group assignments, which can reduce the bias to the greatest extent. In the event of a clinical emergency, the principal investigator, sponsor, and other people concerned will decide to remove the blindness.

Besides, Mudan granule and placebo granule are indistinguishable in appearance and taste. During the process of placebo preparation, we consider various factors including the properties, production process, prescription and excipients of the original therapeutic drug. Dextrin, pregelatinized starch and microcrystalline cellulose are admixed in varying proportions. As the original therapeutic drug taste bitter, so sucrose octaacetate is added to rectify the taste. The final color results from the addition of food-grade natural caramel pigment. Lastly, Mudan granule and placebo granule are concealed in uniform packages with the same labels.

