### Safety Assessment

Adverse events coded using MedDRA prepared by the ICH will be tabulated and described. Comparisons between groups of the incidence of adverse events will be employed by the χ^2^ test or the Fisher exact test. Meanwhile, statistical description of the normal/abnormal changes of laboratory test results before and after administration of Mudan granule in each group and their relationship with Mudan granule will be described in detail.

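### The Safety Set is defined by receipt of Mudan granule, which read literally leaves out the placebo arm and contradicts the planned between-group adverse-event comparison; probably a wording slip, but it needs correcting

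*Protocol article*

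**What the plan says.** The section Definition and Selection of Statistical Analysis Data Set names three analysis sets. The third, and the only one for safety, reads: "SS includes all subjects who are block randomized, receive at least one dose of Mudan granule, and have at least one postbaseline safety evaluation". All three conditions must be met together.

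Intervention Measures sets out what each arm takes. One arm is "the intervention group (Mudan granule 7 g/bag, three times per day"); the alternative is "or the control group (placebo 7 g/bag, three times per day) through a central randomization system". The background treatment is common to both: "All included subjects will accept conventional therapies containing 0.5 mg oral methylcobalamin tablets three times per day". The Blinding section describes the placebo as excipients with a taste agent and a pigment: "Dextrin, pregelatinized starch and microcrystalline cellulose are admixed in varying proportions".

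Safety Assessment then states: "Comparisons between groups of the incidence of adverse events will be employed by the χ^2^ test or the Fisher exact test". The same section goes on to describe laboratory changes around administration of Mudan granule in each of the two groups.

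Blind Review and Database Lock assigns every subject to analysis sets at the blind review. Under Unblinding, the statisticians first receive only the codes A and B, and learn which is which at the summary meeting, after their report has been prepared.

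**The concern.** An analysis-set definition is the operative rule for who is counted. Here the rule turns on having taken the active product, which only one arm is given, while the planned analysis compares two arms. Safety is a stated objective of the trial alongside efficacy (Study Objectives), and no second safety population is available to fall back on. If the sentence stands, the analyst must either follow it and report one arm without a comparator, or depart from it and decide after the fact what was meant. Neither is a good position for a prespecified safety analysis.

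**Working it through.** The article states no figure that depends on this definition, so there is nothing to reproduce. The check is to apply the rule to the two arms and see whether the planned test can be run.

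**Inputs**
- Randomised: 402, of whom 201 per arm (Sample Size Calculation).
- Intervention arm: Mudan granule plus methylcobalamin. Control arm: placebo granule plus methylcobalamin (Intervention Measures).
- Placebo contains excipients only (Blinding).
- Planned test: chi-squared or Fisher exact, between groups (Safety Assessment).

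**Step 1. Largest possible Safety Set, all subjects dosed as allocated**

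| Dosing condition | Intervention | Control | Total |
|---|---|---|---|
| Mudan granule, as written | 201 | 0 | 201 + 0 = 201 |
| Mudan granule or placebo | 201 | 201 | 201 + 201 = 402 |

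The literal rule therefore leaves out up to 201 of 402 subjects, that is 201/402 = 50% of the trial and 100% of the controls. The only control who could enter is one given the active granule by a dispensing error.

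**Step 2. The planned test on the literal set**

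Assume for illustration that 20 of 201 intervention subjects have an event; the conclusion is the same for any count. The table is 20 with and 181 without an event in the intervention row, and 0 and 0 in the control row.
- Chi-squared: the expected count is row total × column total / N. For the control row this is 0 × 20/201 = 0 and 0 × 181/201 = 0, so the statistic cannot be computed. The software stopped with a zero-expected-count error.
- Fisher exact: the odds ratio is undefined (returned as nan) and p is trivially 1.0.

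With both arms in the set, either test can be run.

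**Step 3. The rule against the blinding procedure**
- Set membership is decided at the blind review by people who do not know allocation.
- Whether a subject took Mudan granule or placebo is exactly what they do not know, so the literal condition cannot be evaluated at that point.
- The first unblinding gives only A or B, which does not identify the active arm either.
- If a list of Mudan recipients were supplied at that stage, it would consist essentially of one letter and would disclose the code ahead of the second unblinding.

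The definition therefore conflicts with Safety Assessment on the comparison and with Blind Review and Unblinding on how the set is formed.

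**The case against.** The strongest reply is that this is a drafting slip whose meaning is clear from the rest of the article. Primary Outcomes and Secondary Outcomes describe changes in both groups before and after Mudan granule administration, and Safety Assessment does the same for laboratory results. In those places the name can only mean the blinded granule given in either arm. The literal reading also cannot be carried out under the blinding procedure, so the one workable reading is a dose of the assigned granule. Adverse events are collected from enrolled subjects without regard to arm, and Safety Assessment does not itself name the Safety Set.

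Most of this stands. It makes a slip very probable, and a real loss of 201 subjects' data unlikely. A reader might infer that the comparison simply cannot be done; that is true only if the sentence is applied literally, and the rest of the article points away from doing so. It does not make the sentence right. The article nowhere says that the product name means study medication, it names the two products separately when describing the arms and the placebo, and it gives no other safety population. Nor is this a detail left to an unseen analysis plan: the definition is stated here, and stated wrongly.

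A reader might also infer that the post-baseline safety evaluation condition drops everyone lost before the first 4-week visit and so biases adverse-event incidence downward. The documents do not support this, for three reasons.
- The section on safety outcomes and adverse events monitors from enrolment and records events whenever they occur. The definition does not require a scheduled visit, so an early reported event can count as an evaluation.
- If e of n subjects have an event and m subjects with no recorded event are removed, the observed incidence goes from e/n to e/(n − m), which is higher when e and m are positive. Downward bias would need unrecorded events among those removed, and nothing in the article shows that.
- The 20% in Sample Size Calculation is a ceiling on expected withdrawal over the whole trial. It says nothing about loss before week 4.

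**Conclusion.** The Safety Set definition is wrong as written. Taken literally, it excludes every control subject dosed as allocated (up to 201 of 402), contradicts the between-group adverse-event comparison and cannot be applied at the blind review. The count assumes full recruitment to 402 and no dispensing errors. It measures the literal rule, not an expected loss of data, since the intended set very probably covers both arms. The error is one of wording in an operative rule. It should be corrected because the safety comparison depends on this set and the text offers no definition that would settle the meaning. The finding does not extend to the post-baseline condition.

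**What to change.** Define the Safety Set as all randomised subjects who receive at least one dose of study medication (Mudan granule or placebo), leaving the post-baseline condition as it is unless the sponsor prefers to drop it. Replace the product name with study medication in the section on safety outcomes and adverse events, where relationship to treatment is recorded, and in Safety Assessment, where laboratory changes and their relationship to treatment are described. It would also help to state in Safety Assessment that the comparison uses the Safety Set.

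The cost is one sentence in the set definition and matching words in two sections. Sample size, visits and data collection are unchanged. Current Status says that recruitment has not begun, so the correction can be made before any subject is enrolled.

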### Blind Review and Database Lock

After the last eCRF entering into the EDC system and all problematic data resolved, the principal researchers, sponsors, statisticians and data administrators will conduct a blind review. Blind review needs to determine which analysis set each case belonging to and how to deal with missing values and outliers.

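### As worded, the Safety Set admits only subjects who took Mudan granule, so the planned adverse-event comparison has no control group

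*Protocol article*

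**What the plan says.** The Safety Set is the third analysis set in the section Definition and Selection of Statistical Analysis Data Set: "SS includes all subjects who are block randomized, receive at least one dose of Mudan granule", "and have at least one postbaseline safety evaluation". The conditions are cumulative.

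Under Intervention Measures the arms differ only in the granule: "the intervention group (Mudan granule 7 g/bag, three times per day" on one side and "the control group (placebo 7 g/bag, three times per day" on the other. Both arms take methylcobalamin.

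The Safety Assessment section then plans a two-arm test: "Comparisons between groups of the incidence of adverse events will be employed by" a chi-squared or Fisher exact test. It also describes laboratory changes in each group, dated from the taking of Mudan granule.

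On timing, the section Blind Review and Database Lock states: "Blind review needs to determine which analysis set each case belonging to". Under Unblinding, the statisticians first receive only A/B codes. Which code is the intervention is disclosed at a second unblinding, at the summary meeting.

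**The concern.** Having taken the active product is a condition of entry to the Safety Set, and the control arm is not given the active product. The definition therefore removes the comparator from the safety analysis of a placebo-controlled trial whose stated objective covers safety as well as efficacy.

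If the sentence were followed, adverse events and laboratory changes would be summarised for the Mudan arm alone. Events arising from diabetes, its other treatments or methylcobalamin could then not be separated from effects of Mudan granule.

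There is also a procedural conflict. A rule that asks whether a subject took Mudan cannot be applied by people who do not know the allocation. Applying it at blind review would reveal every subject's arm before the planned unblinding.

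**Working it through.** This is a question of definition, so the check is to apply the rule to the planned arms and count who can enter.

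**Inputs**
- Planned size (Sample Size Calculation): "the target sample size is set at 402, with 201 cases in each group".
- Granule by arm (Intervention Measures): Mudan in the intervention arm, placebo in the control arm.
- Entry rule (Safety Set): randomised, AND at least one dose of Mudan, AND at least one post-baseline safety evaluation. The third condition can only shrink the set; it cannot bring back someone who fails the second.

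**Rule as written**
- Intervention arm: at most 201.
- Control arm: planned Mudan doses = 0, so 0 of 201 qualify. A control could enter only after receiving Mudan in error.
- Excluded by the wording alone: 201/402 = 50% of randomised subjects, and 201/201 = 100% of the control arm.

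**Effect on the planned test**
- The adverse-event table has a control row total of 0. Each expected count in that row is 0 × (column total) / N = 0, so the chi-squared statistic is undefined.
- With a row margin of 0, only one table is possible given the margins, so Fisher's exact test carries no information.

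**Rule with study medication in place of Mudan granule**
- Up to 201 in each arm, 201 + 201 = 402 in total, and the test can be run.

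**Does another provision rescue it?**
- No section adds placebo recipients to the Safety Set or names a different set for safety.
- The Full Analysis Set is a poor substitute because it requires a post-baseline efficacy result. The first one scheduled is the TCM syndrome score at week 4, so subjects who leave before then, including for adverse events, would normally be lost.

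**Can the rule be applied when the protocol says?**
- Membership is fixed at blind review, before the A/B codes are released.
- Even A/B codes do not show which group took Mudan; that waits for the second unblinding.
- A rule based on having taken any blinded granule needs no code and can be applied at blind review.

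**The case against.** The best reply is that this is a slip of terminology whose meaning can be recovered. The article repeatedly writes Mudan granule where it must mean the blinded study medication. The primary and secondary outcomes are compared in both groups before and after its administration, and the Safety Assessment section speaks of it in each group. Nobody would conclude that the primary endpoint lacks a control arm. The Safety Assessment section plainly intends a two-arm comparison, adverse events are collected from all enrolled subjects, and a rule that cannot be applied blind is unlikely to be applied literally. On this view the figure of 201 excluded describes a reading and does not forecast a loss.

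Much of this stands. A slip is very probably the cause, no safety data would go uncollected, and the figures describe the text as written.

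It does not remove the defect. In the outcome and laboratory passages the loose wording only marks a point in time. In the Safety Set it is a condition that decides whose data are analysed, and such a rule should be executable without guessing the intent. If the line is copied into programming specifications, the control arm is dropped. If it is silently reinterpreted, the reported set departs from the published definition.

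It is also fair to say that the article does not contradict analysis by treatment received. That is a standard accompaniment to the correction and not part of the error.

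**Conclusion.** The definition is wrong as written. Followed literally, it leaves 0 of 201 control subjects in the Safety Set, excludes half of the 402 randomised subjects, and contradicts both the planned between-group adverse-event test and the blinded assignment of analysis sets.

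This rests on the stated text and on controls receiving no Mudan granule, as planned. It does not assume that the sponsor intended a one-arm safety analysis; the rest of the article points the other way. The statistical analysis plan is not available, so whether it carries the same wording is unknown. The point is not one of missing detail: the rule is stated explicitly and should be corrected before sets are assigned.

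**What to change.** In the Safety Set definition, replace the dosing condition with receipt of at least one dose of study medication (Mudan granule or placebo granule), keep the other two conditions, and state that subjects are analysed by the treatment actually received. Membership can then be decided blind; grouping by treatment received follows once the codes are released.

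In Safety Assessment, refer to administration of study medication where the text now names Mudan granule for both groups. The same change in the outcome descriptions would make usage consistent, although nothing in the analysis depends on it there. Check the statistical analysis plan for the same definition and correct it if present.

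The cost is a few words of text. No subjects, data, endpoints or analyses change, and the article describes the trial as not yet recruiting.
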